## Overall Description of the Experiment

The proposed study is a 6 mo. study to be completed over a period of 2 yrs. The study will involve 60 overweight healthy male and female volunteers divided into four equal groups matched for age and gender. As shown in figure 1, the four groups include:

Group 1: Controls (No CR but receiving a healthy diet as per the American Heart Association recommendations)

Group 2: CR (energy deficit 25%)

Group 3: CR 12.5% + PA 12.5% (energy deficit 25%)

Group 4: CR (LCD 800 kcal balanced liquid diet) followed after a 15% wt. reduction by wt. maintenance (“wt. clamping”).

**Figure 1**

; 6-

mo

Experimental Design

Time

0

1

2

3

4

5

6

mo

.

Control

25% CR

12.5%CR +

12.5% PA

LCD 800 kcal/d

-15% wt,

CR alone

Randomization

Feeding at PBRC

Green blocks denote metabolic test periods at baseline, 3 and 6 month periods (doubly labeled water plus 5-day inpatient stay (3 weeks total). Yellow blocks denote doubly labeled water measurements only (2 weeks).

This study is to test the feasibility and compliance to a 25% CR diet using several creative strategies, and to pilot and test several of the methods for a subsequent longer calorie restriction study. These include methods for assessing PA under free-living conditions, refinement of the assessments of the neuroendocrine axes, validation of the measure used to assess DNA oxidative stress, and final selection of the genes for tissue mRNA measurements. Because of the tight control of diet and exercise program, it will be impossible to blind all study personnel to the intervention assignment. However, most of the personnel performing the assessment measures (for ex. lab work, DEXA, energy expenditure etc.) will be blinded.

It is anticipated that compliance will be difficult for the volunteers and difficult to assess. Because of this, and in an attempt to improve the ease of compliance and to encourage it, all the volunteers will receive their meals at the Center for the initial 3.5 mos., and during the metabolic testing days. Compliance, however, will still be difficult to assess, since the measured parameters, including body weight, body composition, energy expenditure, dietary records, etc. are insufficiently precise or accurate to provide real-time objective information about it. Therefore, we have included a “weight clamped” group of subjects who have lost 15% of body weight by medically supervised LCD. This will allow the outcomes of interest to be assessed in a group of volunteers who will precisely maintain a new energy balance at an intake predicted to be 20-25% below their baseline energy requirements after rapid wt. loss (15%).

Screening of Subjects, Diet, Exercise Regimen and Behavioral intervention

***Screening paradigm***

Following a brief telephone interview, prospective volunteers will be invited for a series of 3 screening visits to the Center**.**

*Screening visit one*includes explanation and signing of the informed consent. At this visit volunteers will have height, weight, and blood pressure recorded, and complete a brief personal and family medical history and eligibility questionnaire. Potential participants will be interviewed by the psychology staff using the SCID and IDED-IV to identify people who have a history of psychosis, major depression, eating disorders, or another psychiatric problem that might adversely impact participation in the study. Also, the psychology staff will assess motivation to change dietary and exercise habits and to attend feeding and counseling sessions. Potential volunteers will be administered an adaptation of the Motivation and Readiness Scale to measure intention to adhere to various aspects of the intervention. Furthermore, they will be interviewed regarding potential obstacles to participation in the study, e.g., work schedule, family responsibilities, travel schedule, and driving distance to PBRC**.** A demographic questionnaire will also be administered.

*Screening visit two*includes a physical exam, ECG, and distribution of dietary/PA questionnaires**.**

*Screening visit three*includes urine and blood samples for CBC, chemistry panel with electrolytes, urine analysis, and careful review of the diet and PA diaries.

*Between screening sessions*, participants will be instructed to self-monitor all foods they consume and all exercise sessions for two weeks. Structured self-monitoring booklets will be provided to facilitate the completion of this task. To be eligible for the study, participants must complete and bring (to session 3) the self-monitoring records for at least 12 of 14 days (85%). Participants failing to meet this criterion will be provided an additional two weeks to complete this task. If they fail to meet the requirement of this "behavioral run-in", the participants will be excluded from the study. Using these rigorous screening criteria, only highly motivated persons, with few obstacles to participation will be enrolled in the study.

If all of the above visits are completed successfully, the potential volunteer will be invited to participate in this study and will have a final session to discuss all the study requirements. Subjects will then enroll in the dietary portion of the baseline study and undergo 19 days of testing. At the end of the baseline-testing period, volunteers will be randomized to one of the four groups (see Figure 1).

***Diets and diet delivery***

Volunteers will receive a diet based on the American Heart Association guidelines, providing 30% of the calories from fat, 55% from carbohydrate and 15% from protein 116. The diets will consist of three meals and an evening snack arranged in a 5-day rotating menu that will vary as the study proceeds. All foods will beprepared and measured by the Pennington metabolic kitchen staff. The volunteers will be provided with all of their meals bythe MetabolicKitchen, and will be encouraged to consume all food provided. The volunteers will be required to consume breakfast and dinner at the PBRC dining facility on weekdays. Weekday lunches and snacks will be packaged for take-out and will be distributed at breakfast and dinner. Weekend meals will be packaged and distributed at the Friday dinner. In our experience, most volunteers find a 30% fat diet quite filling, since they usually eat a high fat diet with a much lower food volume. We will include bulky foods such as salads and whole grains. Since the volume of food plays an important role in satiation 106, we anticipate that this diet will limit the feeling of hunger during the CR. On the other hand, it may prove difficult to maintain body weight in subjects enrolled in the control group. During the baseline period volunteers will be started on the energy level that most closely matches their estimated energy requirement according to the Schofield equation for RMR and an estimate of PA level as per WHO 117. Each study diet will be prepared at five energy levels (1800, 2200, 2600, 3000, and 3400 kcal/day). For energy levels between these values, subjects will receive 100 kcal "unit" foods to include cookies, breads, and muffins, meeting the nutrient specification of the diet. Subjects will be allowed limited choices of seasonings and beverages within their assigned dietary treatment. Beverages containing caffeine will be limited to less than 5 cups per day. Alcohol will not be served at our facility, but will be allowed in moderation. Subjects will be encouraged to record any deviations from the diet and the consumption of self-selected food and beverage items in a food diary.

After baseline testing and randomization, the target calorie level for each participant is determined. This is achieved by measuring energy expenditure by doubly labeled water (twice at baseline, once whilst the participant is consuming usual diet at home, and once whilst consuming meals provided by PBRC metabolic kitchens) and by the metabolic chamber, baseline feeding requirements and the assigned study intervention. The LCD participants will be fed 800kcal/day regardless of energy requirements until 15% weight loss is achieved. Following this the “weight clamped” subjects will be fed or prescribed a similar diet providing the necessary energy to maintain the 15% wt. loss. Subjects receiving less than 1800 kcals/day will be provided with a multi-vitamin supplement to ensure adequate nutrition is maintained during energy restriction. This will be monitored by pill counts each month.

*Menu Development*. Menus are developed by the metabolic kitchen research dietitians, and are analyzed using the MENu (Moore's Extended Nutrient) database. Recipes are selected to include regional food preferences to increase dietary adherence. The research dietitian reviews the finalized menu with each potential participant before the research project begins. The participant's food likes, dislikes and intolerances, including food allergies, are discussed. If necessary, foods that a participant refuses to eat are substituted with an equivalent food item. Individual choices, within study limitations, are given for beverages throughout the study.

*Diet Distribution*. Daily food production sheets for each participant are used, listing day, menu cycle, meal, food items required with portion weights, and special dietary requirements. When preparing the meal trays, the food production sheets are followed. Additionally, foods are labeled for participant identification. Foods are placed on individual meal trays until served, or are individually packaged for take-out, following tray assembly forms. At the time of meal pick-up, the hostess reviews the menu with the participant, checking off the foods to confirm all are provided. Meals are served to the participant on test days only after all study procedures have been completed. A meal ticket is given to the participant by an authorized nurse or scientist, which is presented to the hostess.

Each participant completes a Daily Food Diary to assist with compliance assessment. The participant is asked to record study foods not eaten, non-study foods eaten, beverages consumed, number of unit foods eaten, and other study-specific food consumption information. The dietetic coordinator reviews the Daily Food Diaries and compiles a compliance score for each participant. Additionally, the dietetic research associates obtain daily comments from each participant, and record dietary progress notes. Potential problems with meal acceptance are identified and resolved. All staff members throughout the study provide personal attention and encouragement to continue on the diets. The first 3.5 mos. of complete feeding at the Center will be used to teach volunteers to comply with the diet while in free-living feeding.

*Low-Calorie Diet.*  Creating a 15% wt. loss in overweight individuals is relatively unexplored. Drawing from the obesity literature, an 800-kcal/d diet with 70g of high quality protein delivered in calorie controlled liquid portions is likely to give optimal weight loss with minimal hunger. Since subjects with a BMI between 25 and 30kg/m2 will have a smaller caloric deficit than obese, it may require up to 10 weeks to reach a 15% wt. loss.

The main safety concern with very low calorie diets is a life threatening cardiac arrhythmia. This complication was first reported in young healthy women following 300-400 kcal/d liquid diets for an average of 5 mos. 118. At autopsy the hearts of these women resembled the protein-depleted hearts of victims who did not survive concentration camps. Since lean subjects conserve protein less efficiently than the obese, one must take precautions to avoid this complication 119,120. Further studies have shown that life-threatening arrhythmias are preceded by a drop in QRS voltage followed by a prolongation of the QT interval 121. A drop in QRS voltage has been seen only in diets of less than 600-kcal/d 122. Since one would expect an increase in QRS voltage with weight loss, a drop in voltage should be a sensitive test to screen for nascent cardiac toxicity of the diet 123. Gallstones are also a potential risk with rapid wt. loss 124. This risk, however, appears to be related to gallbladder stasis that can be avoided by including 10g of fat with one meal each day 125.

Subjects will be placed on an 800-kcal/d diet divided into 5 liquid portions (HEALTHONE). The diet will contain 70g of high quality protein, RDA of vitamins and minerals, 10g of fat with one meal and the remaining macronutrients as carbohydrate. Like the other 3 groups, subjects in this group will come to the metabolic kitchen every weekday to consume breakfast and dinner. The other liquid portions will be distributed daily to be consumed at home. Weekend meal replacements will be distributed Friday evening. Subjects will be seen in the clinic for measures of diet adherence, postural vital signs and metabolic weight once per week. Blood will be drawn and an electrocardiogram performed every 2 wks. If the chemistry panel shows potassium level below normal range, supplementation will be given. Upon achieving a 15% wt. loss, subjects will be progressively put back on solid food (same diet as other groups) in order to maintain the wt. loss. Subjects not attaining a 15% wt. loss by 14 wks. will be judged non-compliant and discharged**.**

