Individual tailoring of treatment. One aspect of lifestyle behavior modification, i.e. frequent and regular therapeutic contact, has been found to be very important for long-term behavior change. To accomplish frequent contact, treatment will be tailored to the needs of the individual participant using internet-based contact and/or telephone contact. Also, for persons who are having difficulty following the prescribed dietary or PA program, the intervention will be tailored to address the unique problems of the individual. The rate of predicted weight loss will be calculated using a 2-reservoir dynamic model of the energy balance equation as described by Alpert 128. This data will be used to monitor compliance and will not be shared with the volunteer. Metabolic weight will be measured once per week. Participants who fail to meet 60% of the expected rate of wt. loss will be interviewed very carefully to identify reasons for potential sup-optimal compliance with the prescribed treatment. Compliance will also be assessed by measures of metabolic rate, heart rate monitors, accelerometers and doubly labeled water. If problems related to compliance are identified, solutions to the problem will be established and individualized interventions will be initiated and tested for specified periods of time. If these interventions result in hypothesized changes in weight, they will be continued; if not, new strategies will be formulated and tested until success is achieved. Only after different tries, subjects will be asked to leave the study.

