The Pennington Metabolic Kitchen staff will prepare all food consumed in the chamber. At baseline, the energy content will be estimated according to a previously developed equation and adjusted during the day on the basis of the energy expenditure of the first 7 hrs. of measurement 156. After the baseline recording, energy content of the food for the subsequent chamber measures will be calculated as 100%, 87.5%, or 75% of baseline 24-h measured energy expenditure, according to the study arm. 24-h urine will be collected for norepinephrine and cortisol excretion rates determinations. During each stay in the chamber, subjects will be asked to fill visual analogue scale (VAS) to measure hunger, satiety, fullness and desire to eat during the course of the day. These VAS tools, first developed by Blundell have been fully validated 157 and used in association with plasma leptin changes in relation to daily changes in hunger and satiety 158. Core temp. will be measured and recorded every 5-min. during the 24 hrs. of energy expenditure measurements in the chamber. At 7:00 AM the volunteers will swallow a 10 x 20-mm silicone coated radio-capsule (Human Technologies, Inc St Petersburg, FL) and will be fitted with a bandoleer type antenna system, connected to a portable monitor that records core temp.

Doubly-labeled Water*.* On Day 0, a fasting baseline urine sample is collected, a metabolic weight taken and a DEXA scan performed. Following this, subjects will drink from a stock solution with 0.22g/kg total body water (TBW) of H218O (Cambridge Isotopes, Cambridge, MA) and 0.115 g/kg TBW of 2H2O (Isotec Inc., Miamisburg, OH or Cambridge Isotopes, Cambridge, MA), followed by a 100-200ml of tap water used to rinse the dose container. Following 2 voids, two consecutive urine samples are collected (at 4 and 6.5 hours after dosing). For the next 14 days after dosing urine samples are collected each morning after breakfast. On Day14, a metabolic weight and DEXA scan is repeated. Additional DLW measurements may be used to monitor compliance periodically throughout the study (at 1 month for Phase 1). Urine samples will be collected on days 0, 7 and 14 only for these additional measurements.

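### Low-calorie-diet participants short of 15% loss at week 14 are discharged after randomisation with no month-6 testing, so the month-6 comparison of that arm covers only those who reached the target

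*Protocol*

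**What the plan says.** After baseline testing, "volunteers will be randomized to one of the four groups" (Screening paradigm). One group is the LCD arm. Under Diets and diet delivery, "The LCD participants will be fed 800kcal/day regardless of energy requirements until 15% weight loss is achieved". The same section then sets the cut-off: "Subjects not attaining a 15% wt. loss by 14 wks. will be judged non-compliant and discharged".

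The testing schedule is in the Figure 1 legend: "Green blocks denote metabolic test periods at baseline, 3 and 6 month periods". The text after Figure 1 gives the arm's purpose, which is to provide a "group of subjects who have lost 15% of body weight by medically supervised LCD" who then hold a new energy balance.

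For poor compliance in general, the Timeline section (Individual tailoring of treatment) is softer. "Participants who fail to meet 60% of the expected rate of wt. loss will be interviewed very carefully", tailored help follows, and "Only after different tries, subjects will be asked to leave the study". No removal threshold is fixed there.

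Power Calculation and Data Analysis plans two analyses: an ANOVA by treatment group of the change between baseline and the end of the study, and a repeated-measures mixed model fitted by maximum likelihood.

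**The concern.** The rule removes randomised participants from one arm because of a response seen after randomisation. Week 14 falls just after the month-3 tests and well before month 6, so those discharged have no month-6 value. For any contrast involving LCD, the end-of-study ANOVA becomes a comparison of completers selected on weight loss. The Timeline rule can do the same in the other restriction arms, but only at discretion and as a last resort.

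The selecting variable is not neutral. Intake is fixed whatever a person's requirement, so the rate of loss reflects three things: baseline expenditure, its fall under restriction, and over-eating. The rule labels all three non-compliance. Selection on the fall acts directly on the change being analysed. Selection on baseline level matters only if level and change are correlated.

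This is a rule about data collection, so an analysis plan that is not shown here could not repair it.

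**Working it through.** **Is month-6 testing really absent?** This is inferred, not stated in words. The subject-population section uses the same verb for pregnant women leaving the study, and no section describes follow-up tests for anyone discharged. Leaving the study is the natural reading.

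**The plan's own figure.** Table 2 gives 11 per group and 80% power for a 10% difference at 5% within-subject CV.
- SD of change = 5 × √2 = 7.07; d = 10/7.07 = 1.414.
- With three groups and Cohen's minimal-variability pattern, f = 1.414 × √(1/6) = 0.577. The noncentrality is 0.577² × 33 = 11, and power is 0.813.

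The row reproduces, so this is not a sample-size error. Power is not the main loss either. By two-sample t-test, LCD against 15 controls has power 0.962 with 15 LCD participants, 0.927 with 11 and 0.869 with 8.

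**Whom the rule removes.** Slack is the over-eating (kcal/d) a person can have and still lose 15% in 14 weeks (98 days):

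slack = TDEE × (1 − a) − 800 − 0.15 × W × E/98

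W is body weight and TDEE is baseline daily expenditure; the pairs below are illustrative assumptions. The fall in expenditure is a; the protocol's background section expects 10–15%. E is the energy cost of weight loss, assumed to be 7,000–7,700 kcal/kg. At 70 kg the last term is 10.5 × E/98 = 750–825 kcal/d.

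| W (kg) / TDEE (kcal/d) | a | Slack (kcal/d) |
|---|---|---|
| 70 / 2,000 | 10% | 175–250 |
| 70 / 2,000 | 15% | 75–150 |
| 80 / 2,400 | 10% | 417–503 |
| 80 / 2,400 | 15% | 297–383 |
| 70 / 1,900 | 5% | 180–255 |
| 70 / 1,900 | 10% | 85–160 |
| 70 / 1,900 | 15% | −10 to +65 |

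Two results follow:
- Over-eating by 260–290 kcal/d discharges the 70 kg / 2,000 person (maximum slack 250) and keeps the 80 kg / 2,400 person (minimum slack 297). The same lapse has different consequences.
- At 70 kg / 1,900, a fall of 15% instead of 5% removes 190 kcal/d of slack (10% of 1,900). The rule can therefore select on the fall in expenditure itself.

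**How often a fully compliant person fails.** Weeks = 0.15 × W × E / (TDEE × (1 − a) − 800) / 7, for a = 10–15%:
- 85 kg / 2,600: 8.3–9.9 weeks
- 70 kg / 2,000: 10.5–12.8 weeks
- 70 kg / 1,800: 12.8–15.8 weeks (14.4–15.8 at a = 15%)

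Most compliant people pass. A small person with low expenditure may not.

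**Effect on the LCD mean.** The arm has 60/4 = 15 participants. If d are discharged and their mean change differs from that of the retained by D percentage points, the all-randomised mean differs from the retained mean by (d/15) × D.

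| d | D = 2 | D = 5 | D = 10 |
|---|---|---|---|
| 1 (6.7%) | 0.13 | 0.33 | 0.67 |
| 3 (20%) | 0.40 | 1.00 | 2.00 |
| 5 (33%) | 0.67 | 1.67 | 3.33 |

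A second route gives a similar scale. Assume a normal model that removes the lowest 10–40% of weight-loss responders, with correlation 0.3–0.7 between response and change in expenditure. The LCD mean then shifts by 0.06–0.45 SD, or 0.4–3.2 points at SD 7.07. Both grids are assumptions; the documents give neither a discharge rate nor a correlation.

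**What the mixed model keeps.** Month 3 is about week 13.0, so people about to be discharged can supply month-3 data. They would still be on the liquid diet, not weight-clamped. The Energy expenditure section says follow-up chamber meals "will be calculated as 100%, 87.5%, or 75% of baseline 24-h measured energy expenditure, according to the study arm", which does not say what someone on 800 kcal/d receives. The model has no observed month-6 value for them.

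**The case against.** The strongest reply is that the selection is deliberate. LCD is a weight-clamp reference group, and its question is conditional on having lost 15%, in a study that describes itself as mainly descriptive. That stands, and an analysis of 15%-achievers serves the purpose. It justifies ending the diet at week 14 but does not require ending measurement.

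The power section names only CR and CR+PA as the interventions tested, and Table 2 totals assume three groups. That also stands: the powered comparison is untouched. LCD is still a randomised arm, included so that the outcomes can be assessed in it.

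The numbers may also be small. The protocol expects the target within about 10 weeks. If, as it predicts, about two thirds of the loss is fat, and fat costs about 9,400 and lean 1,000–1,800 kcal/kg (assumed), then E is about 6,600–6,870. At 70 kg / 1,800 and a 15% fall the target then takes 13.6–14.1 weeks, so fully compliant failures nearly vanish. But slack at 70 kg / 1,900 still drops from about 270–300 to 80–110 kcal/d as the fall goes from 5% to 15%. The rule still selects on the fall among people who over-eat modestly.

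Finally, month-6 values taken after about 12 weeks off the diet describe the effect of assignment, not adaptation at a clamped weight. That is true, and it is why both analyses are needed.

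**Conclusion.** The concern holds. At month 6 the LCD arm, as measured, is no longer the arm that was randomised, because a fixed post-randomisation cut-off tied to the primary outcome decides who is tested. It should be fixed. The consequence is limited to LCD contrasts and, to a lesser and discretionary extent, to removals under the Timeline rule.

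The shift in the LCD mean is below 1 point if one person in 15 is discharged and could reach 2 to 3 points if three to five are, against a 10% design effect. Those figures rest on an assumed 2 to 10 point difference between discharged and retained participants. The sign is unknown. The conclusion also rests on reading discharge as leaving the study, which the wording supports but does not spell out.

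**What to change.** Reword both the week-14 rule and the Timeline removal rule so that a participant goes off intervention, not off study. Invite those participants to the scheduled month-6 resting metabolic rate, chamber, doubly labelled water and DEXA tests, and analyse them in the arm to which they were assigned. Report an analysis restricted to those who reached 15% alongside, for the weight-clamp question.

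The cost is protocol and consent wording, plus month-6 tests already planned for all 60 participants. Some of those discharged will decline. The as-randomised LCD mean will include people who missed 15%, which is why the achievers analysis stays.
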